# KiVa-SEND: protocol for a two-arm feasibility cluster randomised controlled trial of an adapted anti-bullying programme for special schools

**DOI:** 10.1186/s40814-026-01813-x

**Published:** 2026-04-11

**Keywords:** SEND, Anti-bullying, KiVa, Intervention, Randomised controlled trial, Children, Young people, Intellectual disabilities

## Abstract

**Background:**

Bullying is a public health risk with rates amongst pupils in mainstream school estimated to be about 20–30%. This increases to approximately 25–69% amongst pupils with special educational needs and disabilities (SEND). Combined bullying data from two large studies of children and young people from 144 countries found that the greatest risk factor to becoming a victim of bullying was being ‘different’ to one’s peers. These differences included factors such as physical appearance, physical disability or learning disability. Yet there are currently no evidence-based anti-bullying programmes designed specifically for pupils in special schools, and therefore no randomised controlled trials. This study adapted KiVa – an established and evidence-based Finnish anti-bullying programme of ten, 1.5 h lessons that can be embedded into a school curriculum – into KiVa-SEND, by adjusting the language, activities and teaching delivery.

**Methods:**

A two-arm feasibility cluster interventional randomised controlled trial with a 1:1 blocked randomisation allocation ratio of schools and an embedded process evaluation. Data will be collected at baseline and at a 12-month follow-up. Eight UK special education schools will participate with between 128 and 384 pupils and between 16 and 96 teachers completing the data questionnaires. A further three to six teachers and up to 10 pupils will participate in the process evaluation interviews or Talking Mats. Talking Mats is a visual tool to support individuals who struggle with communication, to express their thoughts and emotions. Four schools will be allocated to implement KiVa-SEND across the academic year 2025/26 in addition to anti-bullying practice as usual, and four schools will continue with usual practice alone. Primary outcomes will be feasibility outcomes on the topics of recruitment and retention, adherence, staff surveys, pupil surveys and pupil attendance. Secondary outcomes will focus on pupil survey data, teacher survey data, and the differences between KiVa-SEND and the schools’ current anti-bullying programmes. The process evaluation will focus on the topics of recruitment and retention, implementation and adherence of the adapted KiVa programme, engagement and acceptability of/to pupils and staff, and suitability of the outcome measures.

**Discussion:**

This feasibility cluster randomised controlled trial with embedded process evaluation will evaluate the feasibility of delivering KiVa-SEND within a variety of UK special schools, the acceptance of the materials, and the suitability of the outcome measures, for pupils aged 7–14 with a range of primary educational needs and learning disabilities. This will inform the feasibility to later conduct a definitive randomised controlled trial of the effectiveness of KiVa-SEND.

**Trial registration:**

ISRCTN, ISRCTN15516577. Registered 31 March 2025 before any data collection, https://www.isrctn.com/ISRCTN15516577.

## Background

Bullying is a public health risk with rates amongst pupils in mainstream school estimated to be about 20–30%. This increases to approximately 25–69% amongst pupils with special educational needs and disabilities (SEND; [10]), with the higher rates being found for pupils separated from mainstream classes or schools. Bullying involvement (either as a victim, bully, or bully-victim) can have detrimental effects on health, educational and social outcomes [1] with some negative outcomes lasting into adulthood [8]. Although for many children and young people, victimisation occurs at just one or two time points, for some individuals, victimisation persists across time [12]. In 2005, the UK Government acknowledged the complex and significant issue of bullying amongst school-aged children and the following Education and Inspections Act 2006 was enforced which included the legal requirement of every maintained school in England to have a policy in place to prevent all forms of bullying amongst pupils (legislation.gov.uk). An increase in bullying interventions, policies and resources was observed, yet still the UK remains unstandardised in its approach to anti-bullying. Few randomised controlled trials (RCTs) have investigated the effectiveness of any anti-bullying programme or intervention in mainstream schools and in a recent systematic review, it was found that no RCTs have focused on programmes designed specifically for pupils in special schools [3]. Educators in special school contexts may have adapted mainstream school materials, but whether the adapted (or original) materials are suitable or effective with this population has not been evaluated.

Some mainstream school-based anti-bullying interventions have been found to reduce school-level victimisation by, on average, 15–20% with some findings of up to 50% [5]. Programmes such as KiVa [11], a Finnish anti-bullying programme for pupils aged 7–15, are used in mainstream schools, are evidence-based and show effectiveness in reducing victimisation and increasing empathy in UK primary schools [4]. Any pupil can be involved in bullying, yet certain risk factors increase the likelihood of becoming perpetrators and/or victims of bullying. Combined bullying data from two large studies of children and young people from 144 countries found that the greatest risk factor to becoming a victim of bullying was being ‘different’ to one’s peers. These differences included factors such as physical appearance, physical or learning disability, nationality and family-level disadvantage [15, 16]. It is therefore essential to ensure that any resources and programmes used with the most vulnerable pupils such as those with SEND, are appropriate and effective.

The current trial is in response to the lack of understanding and research into anti-bullying programmes for pupils with SEND, a particularly vulnerable population when it comes to bullying involvement. There is a clear lack of evidence-based support, and the need for an RCT to evaluate a potentially suitable intervention. Recently, a preliminary adaptation of two KiVa lessons for use with special school populations was deemed successful with regards to engagement, acceptability and feasibility [2]. The full adaptation is now complete and known as KiVa-SEND.

## Methods

### Aims

The primary aim is to examine the feasibility of the KiVa-SEND anti-bullying programme being delivered successfully by teachers to pupils in special education schools, with a focus on recruitment and retention, implementation and adherence, engagement and acceptability.

The secondary aim is to examine the suitability of potential outcome measures for pupils and staff.

Combined, these will determine the feasibility to later conduct a definitive randomised controlled trial of the effectiveness of KiVa-SEND.

As a feasibility study, no hypotheses are generated. However, the following feasibility outcome data will be collected: Primary outcomes – 1) recruitment and retention, 2) adherence to the programme, 3) staff survey completion, 4) pupil survey completion. Secondary outcomes – 1) pupil self-report data on bullying involvement, 2) staff data on pupil mental health and pupil involvement in bullying, 3) differences in teaching content and action processes to tackle bullying, between all schools’ usual anti-bullying practice, and the KiVa-SEND practice.

### Design

Two-arm feasibility cluster interventional randomised controlled trial with a 1:1 blocked randomisation allocation ratio of schools and an embedded process evaluation. Recruited schools fall within 50 miles from Oxford with baseline data collected in the summer of 2025 and the follow-up data to be collected 12 months later in the summer of 2026, with the KiVa-SEND intervention being delivered throughout the academic year 2025/2026.

### Study setting—schools and participants

Schools: Eight UK special education schools have been recruited. Schools vary in their pupils' primary educational need (including social, emotional & mental health; autism; cognition & learning; moderate learning difficulties) and overall, include a large proportion of pupils with learning disability, either identified from their Education, Health and Care Plan (EHCP) or from the school’s own database. Pupils: Pupils from select classes from year 3 to year 9 (ages 7 – 14) provided baseline data between April – July 2025, and will provide follow-up data between April – July 2026 (when in year 4 – 10, aged 8 – 15). Once schools were recruited, discussions were had with regards to which class groups would participate in the trial. Decisions were based on the age and ability of the pupils to access the KiVa-SEND materials, and the number of classes in the school. Schools were recommended to suggest between 2 and 6 classes to participate. Staff: Data was, and will, also be collected from the teachers at each time point.

Schools opt into the trial, directly to the research team; parents can opt their child out of the research (although in these cases the pupil will still be able to attend the KiVa-SEND lessons if their school is allocated to the intervention), by informing the school, and pupils must tell the researcher they assent to take part in the data collection on the day of data collection. Information letters and opt-out forms were sent out towards the end of March 2025, via the school, to all parents / guardians of eligible pupils. Parents / guardians had a minimum of two weeks to opt their child out of the data collection (although if they did not opt their child out initially but later wish to withdraw their child and any data already collected, this is also possible up to the full anonymisation of the data after the 12-month follow-up).

For the process evaluation, a sub-set of staff and pupils will be invited to take part in interviews (staff and pupils) or a Talking Mats session (pupils). Talking Mats is a visual communication tool that can support individuals who struggle with communication, to express their thoughts and emotions. It uses picture placement on a visual scale (to signify a positive, neutral or negative feeling, for example) about a particular topic of conversation. Separate consent will be required from staff and parents / guardians, and assent must be given by the pupils for these interview sessions.

### Inclusion and exclusion criteria

Schools: Inclusion – 1) special school, 2) within a 50-mile radius of Oxford (to enable our research teams to visit the schools for in-person data collection). Exclusion – 1) mainstream school, 2) opened within the past year (due to small pupil numbers within the school and within class groups, making the school non-representative).

Pupils: Inclusion – 1) attending a special school, 2) aged between 7 and 14 during baseline data collection (for suitability of the programme content). Exclusion—1) pupils who are unable to access the KiVa-SEND materials; for example, those who cannot integrate into a classroom setting or those who cannot access curriculum-style learning, 2) pupils whose parents have opted their child out of data collection, or 3) eligible pupils who joined the school after the baseline data collection.

### Recruitment and retention

The study started 1st October 2024 and will end 30th September 2026. The trial started school recruitment in October 2024 and completed recruitment early March 2025.

The research team created a database of established special schools within a 50-mile radius of Oxford. Schools were recruited via cold calling from the research team, starting with the closest to Oxford and working outwards. Headteachers were informed of all feasibility study processes and school requirements. At the end of the trial, schools will receive a small monetary recompense: the four schools that will be randomly allocated to continue as usual (usual practice) will receive £100 each; the four schools that will be randomly allocated to trial KiVa-SEND with usual practice will receive £275 each in recognition of additional data collection requirements for the research in the intervention arm and for the time taken to adapt their teaching plans to deliver the programme throughout the year. Contact will be kept with all schools throughout the trial to encourage retention.

### Sample size

Data will be collected from 2 – 6 classes per school. With an average of 8 pupils per class, the pupil sample size is 296. With eight schools and a range of 2- 6 classes per school, the teacher sample size is estimated to be between 16 and 96 depending on whether the same teacher is present for the baseline and follow-up data collection. In total, between three and six teachers will participate in the process evaluation interviews, and up to 10 pupils will participate in the process evaluation interviews or Talking Mats. As a feasibility trial to inform a definitive trial we proposed recruiting sufficient schools and pupils to address our feasibility questions, and particularly the question regarding retention of pupils. With a baseline sample size of 296 children and a potential retention rate of 75% (middle of our amber progression thresholds) a 95% CI of 0.05 would be 70%—80% [7]. Recruiting eight schools as stipulated (four in each trial arm), will ensure that even if we experience whole-school drop-out, expected pupil attrition or refusal, or missing pupil or teacher data, we will still be able to conduct our trial with enough data to provide informative findings.

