### Participant timeline

#### Data analysis

As a feasibility trial, most of our outcome data will be descriptive. Missing data will be reported but no imputation will take place. Data will be summarised at baseline and follow-up by trial arm. Exploratory analysis on primary and secondary outcome measures (OBVQ, TSDQ and TPB) will be conducted between trial arms at the follow-up time point, with the baseline as a covariate, whilst considering school clustering. Although we are not testing the effectiveness of the KiVa-SEND programme during this feasibility trial, we shall explore the pupil and teacher survey data descriptively and statistically, to ensure they are viable options to use in a full trial or whether they do not appear appropriate for this cohort.

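### The 70–80% interval that justifies the sample size treats 296 pupils from eight schools as independent, so the stated precision of pupil retention is too favourable

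*Protocol article*

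**What the plan says.** The Design section describes a "Two-arm feasibility cluster interventional randomised controlled trial with a 1:1 blocked randomisation allocation ratio of schools". In the Sample size section, the pupil number comes from class size: "With an average of 8 pupils per class, the pupil sample size is 296". The spread across schools is given as "Data will be collected from 2 – 6 classes per school". The section says that the sample was chosen to answer the feasibility questions, pupil retention above all. Its only quantitative justification takes the 296 pupils at an assumed 75% retention, a value it places mid-amber, and states: "a 95% CI of 0.05 would be 70%—80"%. No ICC, design effect or effective sample size accompanies this.

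The same paragraph adds that eight schools will leave enough data "even if we experience whole-school drop-out". The Data analysis section plans between-arm comparisons of the OBVQ, TSDQ and TPB "whilst considering school clustering". It does not extend this to retention. Table 2 (Progression criteria) scores follow-up pupil data, among pupils still attending the school, as green from 80%, amber at 60–79% and red at 59% or below. It scores retention of schools on a separate row.

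**The concern.** A binomial interval on 296 pupils is right only if one pupil's retention says nothing about that of another pupil in the same school. Here schools are the sampled and randomised unit. They differ in their pupils' primary need, choose which classes take part, and pass the opt-out letters to parents. The paragraph that quotes the interval also foresees whole schools leaving, which would be retention correlated within school. Clustering is recognised for the outcome comparisons but not for the quantity on which the sample size rests.

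At stake is how much weight the retention result can carry. If readers take ±5 points as what the trial delivers, or the results are reported by the same unclustered method, the retention estimate will look firmer than eight schools can make it when the decision on a definitive trial is taken.

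**Working it through.** **Inputs.** From Sample size: n = 296, p = 0.75, 95% confidence, 8 schools, 2–6 classes per school, 8 pupils per class on average. Average school size m = 296/8 = 37. The ICC is not in the protocol, so every ICC below is an assumption.

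**1. Reproduce the stated figure.** Under independence, SE = sqrt(0.75 × 0.25/296) = sqrt(0.1875/296) = 0.0252. Half-width = 1.96 × SE = 0.0493, or ±4.9 points, which rounds to the protocol's 70–80%. Wilson (69.8–79.6%) and Clopper-Pearson (69.7–79.8%) intervals agree closely. The stated interval is therefore the unclustered one.

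**2. Slack in the figure.** For ±0.05 under independence, n = 1.96² × 0.1875/0.05² = 288.1, so 289 pupils. The design effect (DE) that 296 pupils can absorb is 296/288.1 = 1.027. With DE = 1 + (m − 1) × ICC = 1 + 36 × ICC, the largest tolerable ICC is 0.027/36, about 0.0008.

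**3. Interval with clustering.** Half-width = quantile × 0.0252 × sqrt(DE). The quantile is 1.96 (normal) or 2.365 (t on 8 − 1 = 7 degrees of freedom).

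| Assumed school ICC | DE | Effective n | Half-width, normal (95% CI) | Half-width, t on 7 df |
|---|---|---|---|---|
| 0.01 | 1.36 | 218 | ±5.8 (69.2–80.8%) | ±6.9 |
| 0.02 | 1.72 | 172 | ±6.5 (68.5–81.5%) | ±7.8 |
| 0.05 | 2.80 | 106 | ±8.3 (66.7–83.3%) | ±10.0 |
| 0.10 | 4.60 | 64 | ±10.6 (64.4–85.6%) | ±12.8 |

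**4. Sensitivity.**
- Unequal schools: replace m by Σm²/Σm. Illustrative sizes of 16, 16, 32, 40, 48, 48, 48 and 48 (total 296) give Σm²/Σm = 41.7. At ICC 0.05, DE = 1 + 40.7 × 0.05 = 3.04 and the half-width is ±8.6 points on the normal quantile, slightly wider than with equal schools.
- Class as the only level of clustering (m = 8): at ICC 0.05, DE = 1 + 7 × 0.05 = 1.35 and the half-width is ±5.7 points. This is the mild end.

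**5. Against Table 2.** On the normal quantile, the interval at ICC 0.05 runs from 66.7% to 83.3%, and at 0.10 from 64.4% to 85.6%. Each covers most of the 60–79% amber band and passes 80% into green. The comparison is approximate, because the Table 2 row counts only pupils still attending the school and its denominator may be below 296.

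**The case against.** The arithmetic in the protocol is correct for the assumption it makes. This is a feasibility trial without hypotheses, school recruitment has closed and baseline data are in, so no design choice turns on the figure. The ICC is unknown, and at a low ICC, or with clustering only by class, the interval widens by less than a point. How intervals for progression proportions are calculated is often left to a statistical analysis plan, which is not shown.

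Most of this stands, and it limits the size of the point. It does not rescue the figure: an analysis plan could set the right method, but the published precision would still be that of independent pupils. The absence of a clustered interval method from the article is not itself a fault.

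Three stronger readings are tempting and should not be drawn.
- A reader might infer that the protocol claims to separate amber from green and fails to. It makes no such claim. Table 2 sets percentage thresholds with no confidence-interval rule, and the stated upper limit of 80% already touches the green threshold.
- A reader might build a very large ICC by letting a whole school withdraw. Table 2 scores school retention on its own row and pupil follow-up among those still attending, so that scenario mixes two measures. Whole-school loss is mentioned only as a contingency.
- A reader might hold that retention is mainly determined by the school. The documents do not show this: parents opt out individually, and each pupil assents on the day. Correlation within schools is plausible, but its size is unknown.

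**Conclusion.** The point holds as a misstated precision. The 70–80% interval applies to 296 independent pupils and is too narrow for eight schools of about 37 unless the school ICC is at or below about 0.0008. How much too narrow depends on an ICC that the protocol does not give. Over an assumed 0.01 to 0.10 the half-width is ±5.8 to ±10.6 points, or ±6.9 to ±12.8 with t on 7 degrees of freedom, against the stated ±5. These figures rest on schools of equal size and clustering at school level. Towards the upper end of that range, the retention estimate is materially less informative for progression than the protocol says. The conclusion does not make eight schools too few for a feasibility trial, and it changes no threshold or procedure.

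**What to change.** In Sample size, replace the 70–80% statement with an interval adjusted by DE = 1 + (37 − 1) × ICC over a stated ICC range. Wording could be: assuming a school-level ICC between 0.01 and 0.10, 75% retention among 296 pupils in eight schools would be estimated to within about ±6.9 to ±12.8 points (95% CI, t on 7 degrees of freedom). If 70–80% is kept for reference, label it as assuming independent pupils.

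At analysis, report pupil-level retention and follow-up proportions with school-clustered intervals suited to eight clusters. This can be set out in the analysis plan or the results paper; the article says that protocol modifications will be communicated in later publications.

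The cost is one reworded passage and a different interval method. No schools or pupils are added, and the only loss is a less favourable stated precision.

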### Study flowchart

Figure 1 shows the study flowchart from recruitment through the follow-up data collection.

**Fig. 1 Fig1:**
[figure not shown]
Study flow chart

### Randomisation

The eight schools were randomly allocated using blocked randomisation on a 1:1 basis to either implement KiVa-SEND (intervention group) with usual practice or to continue practice as usual only (comparison group) to understand feasibility of including KiVa-SEND. Randomisation was carried out by one of the trial Co-Investigators (RH) who has no contact with the schools and does not know the school names (codes will be used for the randomisation). The Principal Investigator (JB) informed schools of their allocation once baseline data collection was complete.

The research team randomly allocated the schools to a trial arm (intervention or control), but which classes participated from each school was decided upon by the school.

### Blinding

Schools were informed of their allocation after their baseline data were collected. After allocation, the pupils, teachers and principal investigator were not blind to the intervention status. Although all efforts will be made to keep the majority of the researchers blind to the intervention status, it will be difficult to attend the schools for process evaluation and follow-up data collection and remain blind to the allocation status due to classroom and school displays, and pupils and teachers talking about their KiVa-SEND lessons. We will gather data on unblinding of data collection staff at follow-up to inform the feasibility of researcher blinding in a future trial.

### Intervention: KiVa-SEND

KiVa-SEND is adapted from the anti-bullying programme KiVa. KiVa (Kiusaamista Vastaan: ‘against bullying’) is an evidence-based Finnish anti-bullying programme designed for pupils aged 7–15 [11]. It is currently used in mainstream schools in 23 countries across the world. KiVa has three units, Unit One for ages 7–9, Unit Two for ages 10–12 and Unit Three for ages 13–15 and focuses on delivering and discussing topics such as ‘being part of a group’, ‘school environment’, ‘friendships’, ‘emotions’, ‘inclusion and difference’, as well as traditional bullying and cyberbullying, over the period of one academic year. The KiVa programme focuses on the social architecture of bullying situations and centres on influencing positive pupil behaviours whilst also encouraging bystanders to support victims and stand against bullying.

KiVa is made up of two components: universal actions and indicated actions. Universal actions are found at the class level and school level and are taught and encouraged through a fully manualised set of lessons. Indicated actions are scripted strategies for school staff who form the KiVa Team to manage, document and monitor confirmed cases of bullying involvement.

KiVa-SEND (unpublished) is a UK adaptation and extension of KiVa, which has adapted the materials for use in special schools and for pupils with SEND. Whilst the majority of the lessons are based on the original programme, a few additional lessons have been included to better represent the needs of pupils and staff in special schools. In 2023, the first two adapted lessons were co-developed and successfully piloted in two UK special schools [2]. KiVa-SEND is adapted from KiVa Unit One but also includes the cyberbullying components from Unit Two. The adaptation has simplified the language, avoided abstract concepts, and has increased the quantity and variety of interactive activities to cater to a range of learning styles and abilities. It includes new presentation slides to accompany the teaching of every lesson. Many of the lessons do not require a good level of expressive language skill.

KiVa-SEND will be delivered over one academic year (September 2025 – July 2026) and is designed to fit within each school’s Personal, Social, Health and Economic (PSHE) education classes (a total of 20, 45-min lessons). The four schools randomly allocated to deliver KiVa-SEND were provided with training for two or three members of their staff before delivering the programme. They will then be expected to lead the wider school implementation. Adherence to the intervention will be monitored by the research team via end-of-lesson teacher reporting forms which will reflect on which lesson activities were covered, and the reason for non-coverage.

